### Relevant concomitant care and interventions during the trial

During the period of participation in the research, patients will not be allowed to participate in another research protocol involving human beings without having discussed it with the physician following him or her in the context of the research. Nevertheless, patients may participate in other non-interventional research.

At the end of the patients’ participation, no exclusion period will be required.

### Aims

We assume that individual APN intervention, as part of the usual care management of hypertension, can improve hypertension control.

Our primary objective will be:To compare the rate of controlled BP in “intervention” and “usual care” groups

Our secondary objectives will be:To assess adherence to the home BP monitoring protocolTo assess therapeutic adjustments of antihypertensive drugs and their indications (efficacy and/or tolerance) during the APN interventionTo describe the evolution of BP control between the day of hospitalization and the MD consultation in each group.

### Outcomes

All outcomes will be evaluated on a timeframe of 2–12 months depending on the period between the day of hospitalization (inclusion visit) and the MD consultation (final visit of the study).

The primary outcome will be:Rate of controlled BP in MD consultation by office BP measurement

According to the European and International guidelines, the protocol for office BP measurement will be 5 min rest, 3 measurements at 1-min intervals in a supine position followed by 3 standing measurements at 1-min intervals for orthostatic hypotension test [1–4]. Unattended office BP measurement will be conducted by a supervisor (usually a nurse), who will explain the protocol to the patient before letting him rest in a quiet room: an automatic sphygmomanometer that will print the measurement statement at the end of the monitoring session. BP level will be estimated by the average of the last two BP measures in the supine position. BP will be considered as controlled with systolic BP < 140 mmHg and diastolic BP < 90 mmHg [1–4].

As a reminder, only the BP level by office BP measurement during the MD consultation (final visit of the study) will constitute the primary outcome.

The secondary outcomes will be:Rate and quality of home BP monitoring brought to MD consultation.

According to the 2020 International Society of Hypertension (ISH) Global Hypertension Practice Guidelines, the protocol for home BP monitoring will be 3-day monitoring with a cycle of 3 measurements every morning and every evening at 1-min intervals, in a sitting position, after 5 min of rest and before meals [1]. Quality will be assessed by the number of measurements (18 measurements over 3 days).2)Therapeutic adjustments (and their indication(s)) will be collected in the medical file due to the traceability of the prescriptions of antihypertensive treatment and the APN intervention report.3)Difference in rates of controlled BP between day hospitalization and MD consultation in each group. Note that BP level during day hospitalization is measured with the same protocol as during MD consultation.

### Sample size

For primary outcome measurement, according to the preliminary results of our pilot study, we estimated the number of patients to be included in our trial. We made the hypothesis of 50% and 65% of controlled BP in the “usual care” and “intervention” groups, respectively, equivalent to a 30% increase in the rate of controlled hypertensive participants in the “intervention” group (corresponding to a 15% absolute increase or a 30% relative increase in the controlled BP rates). Assuming an equal number of patients in the two groups, a chi-squared test with a 2-sided significance level of 5%, and a power of 85%, it will be necessary to recruit 300 patients (150 per arm). With a 10% margin of loss to follow-up, 330 patients will need to be recruited (165 per arm).

Sample size calculation was performed with the SAS software (version 9.4; Institute Carry, NC).

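### The sample size does not give the stated power: 150 evaluable patients per arm give about 75%, not 85%, for 50% versus 65%

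*Protocol article*

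**What the plan says.** The calculation is in the Sample size section of the protocol article, and every input is given there.

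- **Rates:** "We made the hypothesis of 50% and 65% of controlled BP in the" usual-care and intervention groups respectively, described as "corresponding to a 15% absolute increase or a 30% relative increase in the controlled BP rates".
- **Allocation:** "Assuming an equal number of patients in the two groups".
- **Test, power and result:** "a chi-squared test with a 2-sided significance level of 5%, and a power of 85%, it will be necessary to recruit 300 patients", which the section gives as 150 per arm.
- **Allowance for loss:** a 10% margin is added, giving 330 patients, or 165 per arm.

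The Statistical analysis section agrees with this set-up. The primary comparison is a chi-square test judged at p < 0.05, no interim analysis is planned, and participants without a primary outcome are left out. Power therefore depends on the number of evaluable patients.

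**The concern.** For a 15-point difference around the middle of the probability scale, 150 per arm is too few for 85% power with a two-sided 5% test. The paragraph fixes the rates, the allocation, the test, its sidedness, the level, the power and the number of patients, so it can be checked without outside information. If it fails the check, at least one stated figure is wrong.

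At stake is the chance that the trial misses the effect it was designed to find. The stated power implies a 15% risk of missing a true 15-point gain. If that risk is really about 25%, one such trial in four would end without a significant result, and anyone interpreting that result would be relying on a sensitivity the design does not have.

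**Working it through.** **Inputs** (Sample size section): p1 = 0.50, p2 = 0.65, difference d = 0.15, 1:1 allocation, two-sided alpha = 0.05, power 85%, stated n = 150 per arm.

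**Derived quantities**
- Mean rate = (0.50 + 0.65)/2 = 0.575
- Under the null: sqrt(2 × 0.575 × 0.425) = sqrt(0.48875) = 0.6991
- Under the alternative: sqrt(0.50 × 0.50 + 0.65 × 0.35) = sqrt(0.4775) = 0.6910
- z for two-sided 5% = 1.960; z for 85% power = 1.036; z for 75% power = 0.674

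**Step 1. Try to reproduce 150 per arm at 85% power.** The pooled formula is n = (z_alpha × 0.6991 + z_power × 0.6910)² / d².
- 85% power: (1.3702 + 0.7162)² / 0.0225 = 4.353 / 0.0225 = 193.5, so 194 per arm
- 75% power: (1.3702 + 0.4661)² / 0.0225 = 3.372 / 0.0225 = 149.9, so 150 per arm

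The stated 150 is not reproduced at 85%. It is exactly what this formula returns at 75%.

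**Step 2. Try the other usual formulas for 85%, two-sided.**
- Unpooled: 0.4775 × (1.960 + 1.036)² / 0.0225 = 190.5, so 191 per arm
- Continuity-corrected: 207 per arm

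**Step 3. Power at 150 per arm, two-sided 5%.** Power = Φ[(d × sqrt(n) − z_alpha × 0.6991) / 0.6910] = Φ[(1.8371 − 1.3702) / 0.6910] = Φ(0.676) = 75.0%.

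| Method | Power at 150 per arm |
|---|---|
| Pooled normal | 75.0% |
| Unpooled normal | 75.8% |
| Arcsine | 75.1% |
| Exact enumeration, uncorrected chi-squared | 76.1% |
| Exact enumeration, continuity-corrected | 72.3% |

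**Step 4. Does the allowance for loss rescue it?**
- No loss at all, 165 per arm: 79.0% pooled, 79.3% exact
- 10% loss from 330: 330 × 0.90 = 297 evaluable (148.5 per arm), power 74.6%

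**Step 5. What would make the stated figures agree?**
- A one-sided 5% test gives 84.0% power at 150 per arm and needs 155 per arm (pooled) or 153 (unpooled) for 85%.
- A two-sided test with 150 per arm reaches 85% power when the intervention rate is 67.0%, a difference of 17 points.

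**Step 6. The inflation.** 300 × 1.10 = 330, but 300 / 0.90 = 333.3, so 334 patients are needed to keep 300 after a 10% loss. The 330 planned covers 30/330 = 9.1%.

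**The case against.** Nothing in the document restores the 85%. The numbers in the paragraph are intact and consistent with one another (300 and 150, 330 and 165), so a reading fault does not explain the gap, and the planned analysis is the same two-sided test. Four points on the other side deserve an answer.

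- **Which figure is the slip is unknown.** The power, the number of patients, the sidedness or the assumed rate could be the wrong entry. This stands. The text shows that the set is inconsistent and that, as written, the power is about 75%. It does not show how the error arose.
- **The 330 can be defended as a convention.** Adding a 10% margin to 300 does give 330, and the effect on power is 74.6% against 75.0%. This also stands, and the point is only a side note.
- **The error does no harm to the estimate.** It leaves the type I error, the effect estimate and its confidence interval untouched, and how readers would take a null result is a prediction. That is fair. The demonstrable harm is the understated type II error.
- **Adjusting for baseline might recover some power.** The gain depends on how well baseline control predicts final control, which the article does not report. The Statistical analysis section schedules no such adjustment, so it would mean changing the primary analysis. It cannot be counted on here.

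**Conclusion.** The concern holds. Under the plan's own assumptions, 150 evaluable patients per arm give about 75% power (72% to 76% across the two-sided methods tried), roughly 10 percentage points below the stated 85%. The shortfall against 85% is 41 to 44 evaluable patients per arm, or 82 to 88 in total, too large to come from rounding or choice of formula. Even complete follow-up of all 330 leaves power at 79%.

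This rests only on the stated rates, equal arms and a two-sided 5% chi-squared test. Real power could be lower: the Participants section also lists an acute cardiovascular event, and a change of treatment by another professional, as reasons for dropout, whereas the stated margin is for loss to follow-up only. Because this is a headline property of the primary analysis and it is wrong as written, it must be corrected.

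**What to change.** Rewrite the Sample size paragraph so that its figures agree. There are two consistent routes.

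1. **Keep the numbers and correct the power.** State that 300 evaluable patients (150 per arm) give 75% power for 50% versus 65% with a two-sided 5% chi-squared test, and 85% power for about 50% versus 67%. This costs one paragraph of text and a less favourable power statement; enrolment does not change.
2. **Keep 85% power for 50% versus 65% and correct the numbers.** State 194 evaluable per arm (388 in total). With 10% loss, 194 / 0.90 = 215.6, so 216 per arm, or 432 recruited. This means 102 more patients than the 330 planned (432 − 330) and a longer recruitment period.

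Route 1 is the minimum and is enough to make the document correct, but it means accepting a type II error of about 25%, which should be stated openly. Under either route, check the original software settings for power and sidedness before rewriting. With route 1, also say that 330 allows for a 9.1% loss, or write 334 for a 10% loss.

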### Recruitment

Recruitment will be conducted during the day of hospitalization, by the residents of the unit, according to the recommendations of the study coordinator.

The residents will explain the study protocol to eligible patients, propose to them to participate and give them an information notice and a consent form to sign. Patients will have to indicate if they consent to participate or not (+/− sign the form) before the end of the day of hospitalization.

After having collected the signed consent form, the residents will give the consent form to the APN/MD to countersign before randomization at the end of the hospital day.

### Sequence generation

Block randomization will be conducted by [name], a MD in the unit trained in biostatistics, using the randbetween formula (0 to 100) on the Excel software for Windows, by blocks of variable size. The even numbers will constitute the “intervention” group and the odd numbers the “usual care” group. This method will ensure the homogeneity and unpredictability of the randomization during the study period. No stratification is scheduled.

The randomization list will then be copied onto a permanent registry. Allocation groups will be concealed in individual numbered opaque sealed envelopes (one per participant). The number and allocation for each envelope will be assigned according to the randomization list.

The individual sealed envelopes will be given to the day hospital nurses who will randomize participants. Nurses will never have access to the randomization list.

### Randomization

Day hospital nurses will randomize participants. They will be involved in hypertension management only in the day hospital, neither before nor after, and will have no interest in generating any bias in the randomization.

At the last moment in the day hospital (after patient inclusion and consent form signature), the nurse in charge of scheduling the follow-up appointments will randomize each participant through an individual numbered envelope mentioning the allocation group. According to the allocation group, the nurse will make the following appointments: APN and MD appointments for the “intervention group” or MD appointment only for the “usual care” group. The participants will go home just after receiving their next appointment(s).

Nurses will not be allowed to open the envelopes prior to the randomization or to change the order of the envelopes. Compliance with the randomization list will be verified by the number attributed to each envelope and anomalies will be identified if the randomization sequence has been violated.

### Allocation concealment

As a reminder, this study cannot be blinded because follow-up appointment(s) must be scheduled according to the allocation group.

Nevertheless, allocation concealment is preserved for as long as possible through the individual numbered opaque sealed envelopes and thanks to the nurses who will proceed to randomization as late as possible: just before scheduling the follow-up appointment(s) and sending the patient home.

The investigator and the statistician will never have access to the randomization list.

### Ethical compliance

The study is registered in the French National Agency for Medicines and Health Products Safety (No. 2020-A00158-31).

### Equipment

During the day hospitalization, a tensiometer will be given to all participants, whether they have one at home or not and regardless of their group, the objective being to avoid any measurement bias in home BP monitoring protocol.

The tensiometer meets the recommendations of the French Society of Arterial Hypertension [23].

### Home BP monitoring

A dedicated home BP monitoring sheet with oral and written explanations for home BP monitoring protocol will be given with the tensiometer to all participants during the day of hospitalization. Participants will be asked to perform only one home BP monitoring, a few days before their next follow-up consultation(s): MD consultation for all participants ± APN intervention according to the allocation group.

The home BP monitoring protocol is detailed above in the “Outcomes” section.

No interpretation of the home BP monitoring result will be requested from the participants. Nevertheless, they will be able to contact the unit if they are concerned.

The protocol will be explained again during the APN intervention for the “intervention” group if needed.

### The APN and associated competences

According to the national decree, an APN requires a nurse to have practiced for at least three years and to have obtained a master’s degree.

The APN must not only retain the skills specific to nursing, but also acquire other specific skills for the management of chronic pathologies, including hypertension.

The APN takes care of patients as part of the treatment of their stabilized chronic pathologies. The management of acute events and decompensation for chronic conditions are left to the MD.

Decree n° 2018-629 defines APN competences as “carrying out any clinical evaluation and conclusion act or any clinical and paraclinical surveillance act”; performing reference monitoring, prevention, and technical acts; and renewing medication [22, 24].

### APN intervention

The APN intervention will be scheduled halfway between the day of hospitalization and the MD consultation. The MD consultation will first be scheduled 2–12 months after the day of hospitalization according to usual hypertension management and the APN intervention will then be scheduled 1–6 months after the day of hospitalization according to the time of the MD consultation for the “intervention” group. For example, if the MD consultation is scheduled 8 months after the day of hospitalization, then the APN intervention will be scheduled 4 months after the day of hospitalization. We kept the minimum time for follow-up at 1 month because this is the minimum time needed to reassess the efficacy and tolerance of antihypertensive treatment in case of therapeutic change during the day hospital session.

The APN intervention will always take place in the hospital, at the consultation unit of the Diagnosis and Therapeutic Center of Hôtel-Dieu University Hospital, at the same location as the MD consultation.

The APN intervention will be divided into different stages: examination, discussions, therapeutic education with empowerment, and medication plan (Fig. 2).

**Fig. 2 Fig2:**
[figure not shown]
Plan for the APN intervention

The APN intervention will be performed by the same APN hypertension specialist and will last approximately 45 min to 1 h.

First, the APN will proceed to office BP measurement. The APN will explain the procedure for office BP measurement, check the correct functioning of the automatic sphygmomanometer, and install the patient in a quiet room to minimize unattended results. As described above, office BP will be measured according to the latest recommendations: 5 min of rest without speaking or smoking, 3 measurements at 1-min interval in a supine position followed by 3 measurements in a standing position for orthostatic hypotension test. These measurements will be performed with an oscillometric automatic sphygmomanometer. The retained office BP measurement will be the average of the last two measurements in the supine position [1, 2, 23]. This office BP measurement will be compared to the home BP monitoring measurement. While home BP monitoring is usually considered superior, according to its quality and taking into account potential masked or white coat hypertension, either office BP measurement or home BP monitoring will be preferred by the APN to evaluate the BP level and the efficacy of the antihypertensive drugs taken during the study [1, 2].

Through a clinical exam, the APN will then assess the general statement of health, efficacy, and potential side effects of antihypertensive treatment such as lower limb edema or cough, as well as clinical manifestations of hypertension or its complications such as headache, vertigo, syncope, impaired vision, rest or exertion chest pain, dyspnea, palpitations, intermittent claudication, edema, and cold extremities. The search for side effects will be completed, if necessary, by a cardio-pulmonary auscultation and/or an electrocardiogram (ECG). The APN will immediately refer clinically unstable patients to an MD.

The most recent blood tests will be checked to assess potential side effects of antihypertensive treatment such as dyskalemia or acute kidney injury and/or cardiovascular comorbidities such as diabetes or dyslipidemia according to the latest recommendations [25].

The APN will sum up the medical history, assess the patient’s knowledge and remind him or her of the definition, the pathophysiology, the chronic aspect of hypertension, and its possible complications.

The APN will then assess the lifestyle and advise the patient according to the latest recommendations [1–3, 23]:Salt consumption limitation (about 6 to 8 g a day)Weight reduction in the event of overweight or obesity to maintain a normal body mass index (between 18.5 and 24.9)Practice of regular physical activity of approximately 30 min a day (to be adapted according to the clinical condition of the patient)Alcohol consumption limitation to less than 14 units per week for men, 8 units per week for womenEstablishment of a diet rich in fiber and low in saturated fatSmoking cessation

Patients’ knowledge about drugs, their indications, and mechanisms will be evaluated and updated if necessary. To estimate the overall risk of drug interaction, the APN will ask the patient about a possible additional prescription or self-medication.

While posology adaptation in the event of side effects or uncontrolled hypertension will be carried out when necessary, the APN will refer the patient to the MD if an introduction of a new drug is needed.

The APN will propose to the patient a decision-making balance between benefits and risks, the objective being to encourage the patient to improve therapeutic adherence, to promote a healthy lifestyle, and to establish in coordination with the patient a treatment plan to improve adherence.

The end of the patient interview will be dedicated to unmentioned questions or subjects, requiring in-depth consideration.

The APN will give the patient a new home BP monitoring sheet with a reminder of the procedure to follow. The patient will be required to bring the results to his or her next MD consultation.

The APN intervention report will be digitally available in the patient’s electronic medical file.

If a participant does not show up for the APN intervention, we will call him/her to schedule another appointment in the limit of the data collection timeframe. If he/she still does not show up, the allocation group will remain the same. The rate of participants not having shown up for the APN intervention will be mentioned in the result.

### MD consultation

The MD consultation will be divided into different stages: examination, discussions, and medication plan (Fig. 3).

**Fig. 3 Fig3:**
[figure not shown]
Plan for the MD consultation

Before the MD consultation, a healthcare giver (usually a nurse) will perform an office BP measurement according to the protocol described in the “Outcomes” section. An ECG will likewise be performed before the MD consultation.

The MD will proceed to the physical examination and evaluate drug treatments, tolerance, efficacy, and eventual modifications since the previous appointment.

He will check the home BP monitoring and other paraclinical exams such as ECG or blood test. While home BP monitoring is usually considered superior, according to its quality and taking into account potential masked or white coat hypertension, either the office BP measurement or home BP monitoring will be preferred by the MD to evaluate the BP level and the efficacy of the antihypertensive drugs taken during the study [1, 2].

The MD will carry out a summary of the medical history since the last follow-up, an assessment of the cardiovascular risk factors, and a clinical summary.

Finally, the MD will prescribe medication and paraclinical exams, if needed, for the next appointment.

If a participant does not show up for the MD consultation, we will call him/her to schedule another appointment in the limit of the data collection timeframe. If he/she still does not show up, the participant will be considered lost to follow-up.

### Data collection

All data will be collected on-site, none remotely.

The main criterion will be measured in the framework of a protocol detailed in the “Outcomes” section, supervised by a healthcare giver (usually a nurse), using an automatic sphygmomanometer that can print the statement of measures at the end of the monitoring.

As for the home BP monitoring, even if it is conducted by participants at home, data will be collected on-site during the MD consultation.

Information about therapeutic adjustments will also be collected on-site in medical files.

All information required by the protocol will be recorded on a case report form. An explanation will be provided for any missing data. The data will be collected as obtained and clearly transcribed on the case report form.

Erroneous data found on the case report form will be deleted and the corrected data will be copied, next to the deleted information, accompanied by the initials, the date, and any justification by the investigator or authorized person having made the correction.

The chief investigator and the coordinator will make the final decision to terminate the trial.

